## Abstract

**Introduction:**

Therapeutic physical exercise (TPE) is considered the cornerstone intervention to prevent or reverse frailty; however, prefrail individuals often face challenges achieving the exercise intensity required to induce multisystem adaptations. Non-invasive neuromodulation techniques—including virtual running–based visual illusion (VR) and, transcranial direct current stimulation (tDCS),—have shown promising effects on neuroplasticity, motor performance and executive function. The primary objective of this study is to compare the effect of adding two neuromodulation strategies to a multicomponent TPE programme on functional capacity and quality of life in prefrail older adults.

**Methods and analysis:**

This four-arm, triple-blinded randomized controlled trial will include adults aged ≥ 65 years classified as prefrail according to Fried criteria. Participants will be randomly assigned to one of the following groups: VR+TPE, sham VR+TPE, tDCS+TPE or, sham tDCS+TPE. All interventions will be applied during an 8 week-programme consisting of 24 supervised sessions. The primary outcomes will be frailty status (Fried Phenotype) and walking speed. Secondary outcomes will include neuroplasticity biomarkers (plasma BDNF), heart rate variability, upper and lower limb isometric strength, quality of life (EQ 5D 5L), lower-limb muscle power, static and dynamic functionality, gait quality and dual-task performance. Assessments will be conducted at baseline, immediately after the first session, at 4 weeks, at the end of the 8 week intervention, and at 4 week follow up.

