### Sample size

2.7

Sample size has been calculated *a priori* using a type I error of 5% and a statistical power of 80% using the software GPower 3.1 (Universität Düsseldorf, Germany). Likewise, an effect size that would allow the minimum detectable change reported by Perera et al. (2006) was considered, based on the main variable ‘speed’ of 0.19 m/s, with a standard deviation of 0.29 m/s. Based on these premises, the number of participants required per group is 16. Assuming potential losses of 20%, the necessary sample size will be of 20 participants per group for a total sample of 80 participants.

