### Statistical analysis

2.9

Data analysis will be performed using the statistical program SPSS v29. For all studies, sample normality will be analysed using the Shapiro Wilk test, homoscedasticity using Levene’s test, and sphericity for the intra-subject factor using Mauchly’s test. For the comparison between groups, a mixed- design ANOVA will be used, with the between-subjects factor “group” (with the two groups included in each sub-study) and the intra-subject factor “time” including the five assessments. The dependent variables will be those described in the variable description section. The Bonferroni correction will be used for *post-hoc* comparisons. If there is a potential confounding factor that meets the requirements (independence and homogeneity of the lines) to be analysed as a covariate, ANCOVA will be used. The possible heterogeneity of the samples from each pair of groups (in each sub-study) in the baseline will be analysed using an independent samples One-way ANOVA. Differences will be considered statistically significant when the *p*-value is less than 0.05.

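### Two primary outcomes have no hierarchy or success rule and are each tested at 0.05, so if either one counts, the familywise error in each sub-study exceeds 5%

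*Protocol article*

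**What the plan says.** The abstract of the protocol article names two primary outcomes: "The primary outcomes will be frailty status (Fried Phenotype) and walking speed". Section 2.5.1 lists the same two, without ranking them or saying whether success needs one or both.

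Section 2.7 (Sample size) was calculated "using a type I error of 5% and a statistical power of 80" percent, "based on the main variable" speed. Frailty status has no sizing.

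Section 2.9 (Statistical analysis) describes a mixed-design ANOVA "with the two groups included in each sub-study) and the intra-subject factor “time” including the five assessments". The threshold is general: "Differences will be considered statistically significant when the *p*-value is less than 0.05". The only multiplicity rule is this: "The Bonferroni correction will be used for *post-hoc* comparisons". The section does not say whether the group effect or the group-by-time interaction is decisive, or at which visit.

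**The concern.** Section 2.7 treats walking speed as the one main variable, while the abstract and section 2.5.1 give frailty status equal standing. With two unranked primaries each tested at 0.05, a positive result on either could be reported as a positive primary result. The 5% used for planning then describes one test, not the chance of a false primary claim in that sub-study.

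The same question arises one level up. The hypothesis at the end of the Introduction and the outlook in the Discussion can both be read as satisfied if either VR or tDCS adds benefit. On that reading there are four primary tests behind one conclusion.

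Separately, section 2.1 gives the visits different purposes: acute effect, training adaptation and retention. A significant interaction could reflect any of them, so a reader cannot tell in advance what finding would count as success.

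**Working it through.** **Inputs from the article.** There are two primary outcomes (abstract, section 2.5.1) and two sub-studies, each of two groups (section 2.9). The threshold is 0.05 (section 2.9). Planning used a 5% type I error, 80% power, a difference of 0.19 m/s, SD 0.29 m/s and 16 per group, raised to 20 for 20% losses, 80 in total (section 2.7).

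**The plan's own figures.** 16 / (1 − 0.20) = 20 and 4 × 20 = 80, as stated. The 5% holds for a single test: in a simulation of the two-group, five-visit mixed ANOVA under no effect (16 per group, assumed correlation 0.6 between visits), the interaction test rejected in 4.9% of runs. The 16 itself is not reproduced by a two-sided two-sample t test on 0.19 / 0.29 = 0.655, which needs 38 per group. That is a separate matter and matters here only for the cost of the fix.

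**Assumption.** Success on either primary counts, with one test per outcome per sub-study.

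**Per sub-study, independent outcomes.** 1 − (1 − 0.05)² = 1 − 0.9025 = 9.75%.

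**Allowing for correlation.** Slowness by gait speed is one of the Fried criteria (section 2.5.1.1), so the two outcomes should be positively correlated. The article gives no value, so a range is shown, by simulation of correlated test statistics at 0.05. Trial-wide means any of the four tests. The two sub-studies share no arm, so their tests are independent and the trial-wide figure is 1 − (1 − p)², with p the per-sub-study error.

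| Correlation | Per sub-study | Trial-wide |
|---|---|---|
| 0 | 9.75% (exact) | 18.5% (exact) |
| 0.5 | 9.1% | 17.4% |
| 0.9 | 7.0% | 13.6% |
| 1 | 5% (exact) | 9.75% (exact) |

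The exact trial-wide values are 1 − 0.95⁴ = 18.5% at correlation 0 and 1 − 0.95² = 9.75% at correlation 1. The mixed-ANOVA simulation agrees, with trial-wide rates of 18.7%, 17.3% and 15.0% at outcome correlations of 0, 0.5 and 0.8.

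**Visits.** Within a sub-study and outcome, the group-by-time interaction is one omnibus test over all five assessments, and the comparisons that follow are Bonferroni-corrected. No separate inflation from the number of visits follows from this.

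**The case against.** The strongest reply is that this is a journal article and an unseen analysis plan may rank the primaries or split alpha. Had section 2.9 been silent, that would settle the matter. It is not silent: it fixes 0.05 for all tests and confines Bonferroni to post-hoc comparisons. The article also ranks the outcomes differently in section 2.7 than in the abstract.

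Three further replies stand in part.

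- The 5% in section 2.7 is a planning input for one variable, and the article never promises familywise control. A reader might infer that the stated 5% is simply false. It is not, because each single test holds its level. The excess is familywise.
- The either-outcome rule is not written down. If both primaries had to succeed, the error per sub-study would be at most 5%.
- The two sub-studies concern different interventions, each with its own sham, and share no participants. Treating them as one family is a matter of judgement, so 18.5% is conditional and not the trial's error rate as such.

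A reader might also infer that four post-baseline visits give four uncorrected chances of success. The documents do not support that, given the omnibus interaction test and the Bonferroni correction after it.

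**Conclusion.** The concern holds in a limited form. If success on either primary counts, the familywise error per sub-study is above 5%: about 7% at a correlation of 0.9, about 9% at 0.5, and 9.75% at independence. This rests on the either-outcome assumption and on a correlation the article does not give.

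If one trial-wide claim is drawn from both sub-studies, the range is 9.75% to 18.5%. It is tempting to say that correlation could bring this down to 5%. It cannot, because the sub-studies have no arm in common and even perfectly correlated outcomes leave two independent chances.

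The unnamed deciding effect and visit are a problem of definition. They leave open what the primary result is, but they are not a demonstrated source of further inflation.

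**What to change.** In each sub-study, make walking speed, active against its own sham, the first primary test at 0.05, since the sample size rests on it. Test frailty status at 0.05 only if walking speed is significant. This holds the familywise error at 5% per sub-study without lowering alpha. If the two outcomes are to keep equal rank, use Holm over them instead (smaller p-value against 0.025, then the other against 0.05).

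State in advance which contrast and visit decide. The end of the 8-week intervention (T4) is a natural choice, though section 2.7 names no visit.

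Apply Holm across the two active-sham comparisons only if one trial-wide claim is intended. Without it, the fixed sequence still leaves up to 1 − 0.95² = 9.75% over both sub-studies.

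The cost is more than wording. The trial is registered and ethics-approved with two primaries, so those entries may need updating. Frailty status also cannot be confirmatory where walking speed is not significant. That may be common: on a two-sided two-sample t test with 16 evaluable per group and the section 2.7 inputs, power for walking speed is 43%. Holm has its own price: at 0.025 the same test has 32% power, and would need 46 per group for 80% power instead of 38.

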**Ethics and dissemination:**

The study has received approval from the Ethics Committee of Research in Humans of the University of Valencia (2025-FIS-4007899). All participants will provide written informed consent before enrolment. Study findings will be disseminated through peer reviewed publications, scientific conferences and participant summaries.

**Clinical trial registration:**

https://clinicaltrials.gov/study/NCT07346989?cond=NCT07346989&viewType=Card&rank=1, identifier NCT07346989.

## Introduction

1

The ageing of the population poses a challenge to current public health systems, as people over 65 account for a significant proportion of healthcare expenditure (Sinha, 2011). In fact, as life expectancy increases, so does the prevalence of age-related diseases and disabilities (Lejoyeux et al., 2008). Therefore, the current trend is to promote healthy ageing, making it necessary to identify strategies to prevent disability (Viña and Borrás, 2024).

An example of unhealthy ageing is frailty, a geriatric syndrome that identifies people who are more vulnerable to external stressors, thereby increasing their risk of institutionalization, disability or even death (Fried et al., 2001). The negative effects of frailty are not limited to physical deterioration; they also impact the social, psychological and cognitive spheres of older people, thus reducing their quality of life (Clegg et al., 2013). Frailty is mostly characterized by impairments in the physical domain, such as muscle strength and gait (Pritchard et al., 2017). However, an emerging field of research is focused on the fact that frailty could also be associated with deterioration in brain health (Gutiérrez-Zúñiga et al., 2023), since it has been related to impairment in the brain microstructure (both grey matter and white matter) (Maltais et al., 2020; Tian et al., 2020). In this regard, the reduction of grey matter in specific areas such as the frontal and medial-temporal regions of the brain has been associated with a decrease in walking speed, one of the key criteria for frailty (Callisaya et al., 2014; Rodrigue and Raz, 2004; Rosano et al., 2012).

Furthermore, frailty is associated with a reduction in sensory and motor cortical representation, which affects crucial functions such as sensorimotor coordination, motor function in general, and gait and balance in particular (Carp et al., 2011; Goh, 2011; Koen et al., 2019). This, in turn, leads to a decrease in perceptual impulses, motor actions, and therefore, overall brain stimulation (Dinse, 2006; Mahncke et al., 2006). This causes cortical reorganization, resulting in altered motor patterns, such as motor instability, coordination deficits and decreased movement speed (Dinse, 2006; Mahncke et al., 2006). However, one of the most important characteristics of frailty, from a therapeutic point of view, is that it refers to a dynamic and reversible condition, which means that not all individuals are frail in the same way and, furthermore, a frail individual can become non-frail or robust if frailty is detected and treated, especially in the prefrailty state (Abellan van Kan et al., 2008).

Therapeutic physical exercise (TPE) is the most widely used therapeutic intervention for addressing frailty, especially multicomponent exercise. For TPE to induce multisystemic beneficial effects (including neuroplasticity) and thus improve physical and cognitive status, it must be performed at an appropriate intensity and frequency (World Health Organization, 2010). However, physical limitations and exercise-induced fatigue in frail or prefrail older adults may hinder adherence to such prescriptions (Picorelli et al., 2014). For this reason, other therapeutic strategies are being studied to enhance the results of physical exercise. In this regard, and given that the brain is a highly dynamic organ that exhibits adaptive and maladaptive plasticity (Flor et al., 1995), brain stimulation could be an optimal target for innovative interventions that facilitate ‘executive control of movement,’ focusing on the activation of cortical areas responsible for movement representation, such as motor and premotor areas (Shamsi et al., 2022; Thieme et al., 2018).

Some of these alternatives are mirror neuron activation therapies (MNAT) (motor imagery, action observation, and mirror therapy and/or visual illusion), which have been shown to activate the cortical and subcortical neural networks where mirror neurons are located, enhancing adaptive neuroplasticity mechanisms (Kim and Lee, 2021). In this regard, several studies have demonstrated the beneficial effects of this type of therapeutic intervention on various motor functions in people with diseases such as Parkinson’s (Kwok et al., 2022), after traumatic brain injury (Maggio et al., 2020), stroke (Gandhi et al., 2020; Peng et al., 2019) or spinal cord injury (Moseley, 2007). In the latter population group, our research team has verified how a virtual walking protocol combined with a TPE programme improves their functional capacity and perception of pain. Furthermore, we have recently published a systematic review and meta-analysis showing how MNAT improves functional capacity in older people, although the results when added to TPE are inconclusive, which opens the door to study combined interventions (MNAT + TPE) in frail older people (Mollà-Casanova et al., 2024).

In this context, we recently demonstrated that a visual illusion protocol (i.e., virtual running (VR) combined with TPE improves voluntary movements (i.e., aerobic capacity, lower limb strength and reaction time) in frail and prefrail individuals (Mollà-Casanova et al., 2023). This activation of mirror neurons arises from the activity within the cortical action-perception network that is triggered by the visual stimulus, which engage neuroplastic mechanisms. However, there are different ways to enhance neuroplasticity so, it is highly relevant to explore different therapeutic alternatives in this population, such as transcranial direct current stimulation (tDCS), and to assess their impact on functional variables and to neuroplasticity biomarkers.

Specifically, tDCS consists of applying a weak direct current to the desired cortical area, to modulate brain excitability by shifting the resting membrane potential (Nitsche et al., 2003). In older people, this therapy has been shown to improve aspects of executive function related to movement (Manor et al., 2016; Zhou et al., 2015), but its effectiveness on the functional capacity of frail individuals has not been studied.

Although VR and tDCS both aim to enhance neuroplasticity, they are expected to act through partially distinct neural pathways. VR-based visual illusion primarily engages the action-observation network and mirror neuron system, involving premotor cortex, inferior parietal cortex and sensorimotor integration networks (Kim and Lee, 2021). Conversely, anodal tDCS induces subthreshold modulation of neuronal membrane potentials, facilitating Hebbian plasticity, NMDA-receptor activity and BDNF-dependent synaptic strengthening (Fritsch et al., 2010). Consequently, these interventions may produce distinct neurophysiological adaptations and functional outcomes.

Although several studies have demonstrated additive benefits of combining exercise with neuromodulation techniques in various, these approaches have generally been investigated independently and focused primarily on cognitive aspects, rather than functional. To our knowledge, no randomized controlled trial has directly compared the effect of VR and tDCS when added to a multicomponent exercise programme in parameters related to functional capacity and quality of life in prefrail individuals.

Therefore, this study hypothesizes that adding any of these two therapies (VR and tDCS) to a multicomponent TPE intervention programme will result in additional improvements in parameters related to functional capacity and quality of life in prefrail individuals. This will contribute to preventing the progression toward frailty and, therefore, reducing the social and healthcare costs associated with this condition.

**Objectives:** The general objective of this study is to evaluate the effectiveness of non-invasive neuromodulation combined with a multicomponent TPE programme on variables related to functional capacity and quality of life in prefrail older adults. As specific objectives, the current study seeks to determine the effect of two neuromodulation strategies (i.e., tDCS and VR) combined with a multicomponent TPE programme on gait speed, general physical condition, frailty, static and dynamic functionality and gait quality, upper limb and lower limb isometric strength, quality of life, and neuroplasticity, in terms of plasma BDNF levels, in prefrail older adults.

## Methods and analysis

2

### Design and setting

2.1

This protocol describes a four-arm triple-blinded (participant, outcome assessor, statician) randomised controlled trial that will be conducted in the Faculty of Physiotherapy (University of Valencia). The participants will be randomly allocated into four groups that will be described later: (i) VR + TPE; (ii); sham VR + TPE; (iii) tDCS + TPE and (iv) sham tDCS + TPE. Assessments will be conducted at the following time points: before the first session (T1), immediately after the first session (T2), after 4 weeks of intervention (T3), immediately after the 8-week intervention period (T4) and at 4 week-follow-up (T5). This longitudinal assessment schedule is necessary given the nature of the intervention, which is hypothesized to induce both immediate and experience-dependent neuroplastic changes over time. Early time points (T1–T2) allow the capture of acute neurophysiological and behavioral effects following initial exposure, whereas intermediate and post-intervention assessments (T3–T4) are essential to evaluate progressive training-related adaptations. Finally, the follow-up assessment (T5) enables the examination of the retention and consolidation of treatment-induced effects, providing insight into the durability of potential neuroplastic reorganization. The study design is in accordance with the 2025 Standard Protocol Items: Recommendations for Interventional Trials (SPIRIT) statement (Chan et al., 2025). The flow chart of the study is shown in Figure 1.

**FIGURE 1 F1:**
[figure not shown]
Flowchart of the study design.

### Patient and public involvement

2.2

Participants have participated and will actively participate in the conduct of this study. During the study design phase, feedback was obtained from prefrail and frail individuals participating in a related study conducted by the same research group, and this input informed the refinement of the intervention procedures and study materials. Furthermore, after finishing the study trial, participants will be provided an individual report via email and provided with a summary of the findings and links to the published manuscripts.

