### Participants

2.3

Participants aged over 65 years will be recruited through different older people’s associations (i.e., La Nau Gran and Asociación Grupo de Mayores de Telefónica). The study will also be advertised on the research group website and social media. The researchers will establish compliance with the selection eligibility criteria described in Table 1. Researchers may terminate a participant’s involvement in the study if changes in the participant’s clinical status result in non-compliance with the established eligibility criteria.

**TABLE 1 T1:** Eligibility criteria.

Eligibility Criteria	
**Inclusion criteria**	**1. Exclusion criteria**
Aged over 65 years	History of stroke within the past 6 months or hospital admission for any reason within the past 3 months
Being prefrail according to Fried criteria	Diseases of the central or peripheral nervous system
Ability to understand instructions (Mini-Mental State Examination > 23 points)	Vestibular system
Signing the written informed consent.	Concomitant diseases Have a neurological pathology, cardiovascular musculoskeletal that contraindicates physical activity Epilepsy or history, medications that lower the seizure threshold Cardiac pacemaker, endocranial and hearing implants History of severe headaches Uncontrolled intracranial or arterial hypertension Heart and/or respiratory failure Implanted medication pump Skin lesions (psoriasis, eczema) Serious head surgeries Completing less than 80% of training sessions

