#### Placebo Comparator 1: sham VR + TPE

2.4.2

The intervention will be the same as the former group, yet the video projection will consist of landscapes without featuring any type of human or animal movement, in order not to stimulate the motor areas of the brain.

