If this study demonstrates that VR or tDCS combined with TPE produce greater or comparable improvements relative to TPE alone, the results may suggest the potential clinical value of these approaches as adjunctive interventions. A further strength of this trial is the inclusion of neuroplasticity biomarkers, since it is of great interest to understand the molecular mechanisms involved in the neuroplasticity induced by these types of therapies. There are numerous proteins considered neurotrophic with different functions in the nervous system, such as nerve growth factor (NGF), insulin-like growth factor (IGF-I), neurotrophin 3 (NT-3) and 4/5 (NT 4/5), and brain-derived neurotrophic factor (BDNF) (Noble et al., 2011). The most abundant is BDNF, which stimulates the development and differentiation of new neurons, the survival of existing ones, synapses and neuronal plasticity, promoting long-term potentiation (Miranda et al., 2019). Lower BDNF levels have been associated with frailty and poorer cognitive status (Inglés et al., 2017), and previous research has shown that exercise (Gómez-Pinilla et al., 2002) and tDCS (Fritsch et al., 2010) can independently elevate BDNF. Determining whether their combination yields additive or synergistic effects will provide valuable insights into the neural mechanisms underpinning functional improvements in prefrailty. This biological perspective is especially relevant as interventions that enhance neuroplasticity may also improve cognitive and dual-task performance, both of which are impaired early in the frailty spectrum.

The methodological design of this study—including a four-arm structure, blinding of participants, assessors, and statisticians, and the use of sham controls specific to each technique—ensures a high degree of internal validity. The comprehensive assessment strategy, including questionnaires, objective biomechanical instruments, functional tests and physiological measurements will allow a multidimensional understanding of how neuromodulation influences motor and systemic functions. The addition of dual-task assessments further strengthens the protocol by evaluating cognitive–motor integration, a domain highly relevant to fall risk and functional independence.

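### Table 1 lets in people who already know the active virtual-running procedure, leaving participant blinding in the VR versus sham VR comparison unguarded

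*Protocol article*

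**What the plan says.** Section 2.1 describes a "four-arm triple-blinded (participant, outcome assessor, statician) randomised controlled trial". The Discussion rests the trial's internal validity partly on "blinding of participants, assessors, and statisticians, and the use of sham controls specific to each technique".

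The Introduction reports an earlier study by the same group in which virtual running "combined with TPE improves voluntary movements (i.e., aerobic capacity, lower limb strength and reaction time) in frail and prefrail individuals". Section 2.2 adds that during design "feedback was obtained from prefrail and frail individuals participating in a related study conducted by the same research group", and that "this input informed the refinement of the intervention procedures and study materials".

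On recruitment, section 2.3 names two older people's associations and then states: "The study will also be advertised on the research group website and social media". Table 1 requires prefrailty and lists many medical exclusions. None concerns earlier participation in the group's studies, earlier virtual running or tDCS, or having advised on this trial. The nearest rule, in section 2.4, bars only physiotherapy received at the same time as the trial treatment.

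The active video (2.4.1) shows running legs scaled to the participant's build. In the sham (2.4.2), "the video projection will consist of landscapes without featuring any type of human or animal movement".

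**The concern.** A sham that looks different from the active treatment can still blind, provided that participants do not know which version is the treatment. The VR pair depends on that. A person who has already had virtual running, or who was consulted on the procedures and learned what the active video shows, would lack that ignorance. On seeing running legs or a landscape, they could name their arm at the first session.

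Both primary outcomes are open to this. Walking speed is a maximal-effort test. The Fried phenotype includes self-reported exhaustion, an activity criterion and grip strength. A blinded assessor cannot remove the participant's own expectation. Informed people in the active arm and informed people in the sham arm may also be pushed in opposite directions, so randomisation does not cancel the effect.

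There is a second, smaller consequence. Section 2.1 uses the T1–T2 interval to capture acute effects of a first contact with the intervention, and section 2.5.2.2 records heart rate variability in the first session for a similar purpose. For someone previously given virtual running, session 1 is not a first contact.

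**Working it through.** The plan gives no figure on this point, so the check is mainly a comparison of sections.

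1. **Is participant blinding claimed and relied on?** Yes, in 2.1 and in the Discussion. Section 2.6, which covers blinding, describes safeguards for the evaluator and the analyst only. Evidence that a sham blinds participants is cited in 2.4.4 for tDCS; none is cited in 2.4.2 for the landscape video.
2. **Can the two VR conditions be told apart on sight?** Yes: running legs (2.4.1) against landscapes without human or animal movement (2.4.2).
3. **Do people who may know which is active exist in or near the target population?** Yes. The earlier virtual-running study enrolled frail and prefrail people (Introduction). The people consulted on design were also prefrail and frail (2.2). This trial enrols prefrail people.
4. **Could recruitment reach them?** Yes. The group's own website and social media are among the channels (2.3).
5. **Does any criterion stop them?** No. Table 1 is silent, and the physiotherapy rule in 2.4 concerns concurrent treatment only.

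**Illustration of size (assumptions, not figures from the documents).** Let p be the share of informed people in each VR arm, a the gain in maximal speed among those who know they are in the active arm, and b the loss among those who know they are in sham. The active mean rises by p × a and the sham mean falls by p × b, so the contrast shifts by p × (a + b).

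- The documents plan 20 per arm and a difference of 0.19 m/s (2.7). One to four informed people per arm is 1/20 = 5% to 4/20 = 20%.
- p = 0: shift 0.
- a = b = 0.10 m/s: 0.05 × 0.20 = 0.01 m/s and 0.20 × 0.20 = 0.04 m/s. Against 0.19 m/s these are 0.01/0.19 = 5% and 0.04/0.19 = 21%.
- a = 0.10 m/s, b = 0 (knowing that one is in sham changes nothing): 0.05 × 0.10 = 0.005 m/s and 0.20 × 0.10 = 0.02 m/s, or 3% and 11% of 0.19 m/s.

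The range therefore runs from nothing to about a fifth of the planning difference. The direction follows from the assumption that knowledge helps effort in the active arm or harms it in sham.

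**The case against.** The strongest reply is that nothing in the document is contradicted and no overlap is shown. Section 2.2 speaks only of a related study. It does not say that the study involved virtual running or tDCS, or that contributors saw the running-legs video. Contributors who are still frail are ineligible anyway. The Introduction does not say where the earlier participants came from, how many would still qualify, or whether all of them saw the active video. A fuller protocol could contain the missing criterion. All of this stands, and it is why the point is a risk and not a breach. It does not remove the point: the article prints its eligibility table, and as printed the table admits these people.

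Three stronger readings are tempting and are not supported.

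- *Blinding is already compromised.* The documents do not show that any such person will enrol.
- *Both comparisons are affected.* The argument from the videos applies to the VR pair. The tDCS sham uses a ramp, with cited evidence that it blinds. Only someone who learned of the ramp through the consultation would be affected, and the documents do not say that anyone did.
- *Carry-over from earlier training biases the result.* Randomisation balances earlier training between arms in expectation, every entrant must still be prefrail, and T1 is measured in everyone. Carry-over adds noise; it does not systematically favour an arm.

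It is also fair to say that excluding a few people does not settle whether naive participants can guess their arm. That depends on the consent text, which is not shown, and is a separate question.

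**Conclusion.** The concern holds as an unguarded risk of unknown size, mainly to the VR versus sham VR comparison. The eligibility rule as printed admits people who could identify their arm on sight, in a trial with 20 per arm and with effort-dependent and partly self-reported primary outcomes. For any entrant previously given virtual running, the reading of T1–T2 as a response to first exposure would also fail.

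The illustrative shift of 0 to 0.04 m/s rests wholly on assumed shares and an assumed reaction of 0.10 m/s. It shows the scale on which the risk would matter and is not an estimate. A reader might infer a demonstrated bias in favour of the active arm; the documents do not establish one. This is a cheap improvement of low-to-moderate priority.

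**What to change.** Add one exclusion to Table 1: earlier participation in the group's virtual-running or visual-illusion studies, or having advised on this trial's intervention procedures. Check it at screening against the group's own participant and consultation lists. Record any other earlier exposure to VR or tDCS at baseline, so that it can be described by arm and examined if it turns out not to be rare.

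The cost is one line, a list check and one baseline item. The downside is the loss of a few willing volunteers already known to the group, which could slow recruitment to 80 slightly.
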